## Abstract

**Background:**

Studies suggest that language recovery in aphasia may be improved by pairing speech-language therapy with transcranial direct current stimulation. However, results from many studies have been inconclusive regarding the impact transcranial direct current stimulation may have on language recovery in individuals with aphasia. An important factor that may impact the efficacy of transcranial direct current stimulation is its timing relative to speech-language therapy. Namely, online transcranial direct current stimulation (paired with speech-language therapy) and offline transcranial direct current stimulation (prior to or following speech-language therapy) may have differential effects on language recovery in post-stroke aphasia. Transcranial direct current stimulation provided immediately before speech-language therapy may prime the language system whereas stimulation provided immediately after speech-language therapy may aid in memory consolidation. The main aim of this study is to investigate the differential effects of offline and online transcranial direct stimulation on language recovery (i.e., conversation) in post-stroke aphasia.

**Methods/design:**

The study is a randomized, parallel-assignment, double-blind treatment study. Participants will be randomized to one of four treatment conditions and will participate in 15 treatment sessions. All groups receive speech-language therapy in the form of computer-based script practice. Three groups will receive transcranial direct current stimulation: prior to speech-language therapy, concurrent with speech-language therapy, or following speech-language therapy. One group will receive sham stimulation (speech-language therapy only). We aim to include 12 participants per group (48 total). We will use fMRI-guided neuronavigation to determine placement of transcranial direct stimulation electrodes on participants’ left angular gyrus. Participants will be assessed blindly at baseline, immediately post-treatment, and at 4 weeks and 8 weeks following treatment. The primary outcome measure is change in the rate and accuracy of the trained conversation script from baseline to post-treatment.

**Discussion:**

Results from this study will aid in determining the optimum timing to combine transcranial direct current stimulation with speech-language therapy to facilitate better language outcomes for individuals with aphasia. In addition, effect sizes derived from this study may also inform larger clinical trials investigating the impact of transcranial direct current stimulation on functional communication in individuals with aphasia.

**Trial registration:**

ClinicalTrials.gov NCT03773406. December 12, 2018.

## Background

Aphasia is an acquired (typically left-hemisphere stroke) multi-modality disturbance of language that impacts around 2 million people in the USA and is more common than disorders such as Parkinson’s disease and muscular dystrophy [1]. The disorder impacts not only comprehension and production of oral language but also reading and writing. The consequences of aphasia extend beyond the language impairment and can negatively impact all aspects of the person’s daily life including social, vocational, and recreational activities. Currently, speech-language therapy (SLT) is the most effective way to treat aphasia [2]. However, even if SLT is intensive, individuals with aphasia are left with residual language impairments that impact participation and quality of life. Recent research suggests that language recovery in individuals with aphasia can be boosted by pairing SLT with a non-invasive, safe, and low-cost form of brain stimulation known as transcranial direct current stimulation (tDCS) [3].

In conventional tDCS, direct current is applied to the scalp via two electrodes: an anode and a cathode. tDCS does not induce neuronal firing but modulates the resting membrane potential of the neurons which can then impact the rates at which neurons fire [4]. Early research in animals and human motor cortex established that tDCS effects are polarity specific [4, 5]. Anodal stimulation may increase cortical excitability due to neuronal depolarization while cathodal stimulation decreases cortical excitability due to neuronal hyperpolarization [5].

### tDCS polarity in aphasia

In tDCS studies of aphasia, anodal tDCS is understood to improve performance by increasing cortical excitability while cathodal tDCS impairs performance by decreasing cortical excitability [6, 7]. Therefore, many studies [8–10] have applied anodal tDCS to the left-hemisphere perilesional areas under the assumption that it will upregulate the perilesional areas and improve performance. Other studies [11, 12] have applied cathodal tDCS to homologous right-hemisphere areas under the hypothesis that these areas are maladaptive for language and that downregulating them allows the perilesional left-hemisphere area to process language more efficiently [13].

The notion that anodal tDCS improves performance whereas cathodal tDCS impairs performance is derived primarily from tDCS studies of the motor cortex, and such inferences may not be applicable to language and cognition [14]. The assumption that cathodal tDCS impairs performance is challenged by studies [15–17] that find performance improvements following cathodal tDCS to the left hemisphere. For example, Cherney and colleagues [18] found that cathodal tDCS led to improvement in behavioral measures similar to that of anodal tDCS and significantly more than sham in individuals with aphasia. Moreover, they also found that tDCS to the left hemisphere resulted in an increase in activation of voxels in both hemispheres with more activation in the left perilesional areas. However, studies have differed in terms of stimulation parameters (e.g., timing of tDCS and stimulation intensity). These variations may differentially impact how anodal and cathodal tDCS affect language recovery.

### Stimulation site, intensity, and duration

There is no consensus on the optimal site for stimulation in tDCS studies of aphasia [6]. Some studies [15, 19, 20] have targeted ipsilesional inferior frontal gyrus (IFG) while other studies [11, 21] have targeted contralesional right IFG. Furthermore, other studies have targeted ipsilesional left posterior superior temporal gyrus (pSTG) [9, 12] or contralesional right pSTG [12]. More recently, the cerebellum has also been a site of interest [22, 23]. Most studies have stimulation intensities of 1mA or 2mA with current densities between .029 and 08mA/cm^2^ [6, 24]. The stimulation duration of tDCS studies for aphasia has varied with the majority of studies stimulating for 20 min [6].

### Timing of stimulation

Another critical factor that could determine the efficacy of tDCS is the timing of stimulation and the brain state [25–27]. Studies in healthy individuals have shown that applying offline cathodal tDCS improves behavioral and motor performances [27, 28]. These findings have been explained by the Bienenstock-Cooper-Munro (BCM) principle of homeostatic plasticity [27–29]. According to the BCM theory of “sliding-threshold” for bi-directional plasticity, initial low synaptic activity lowers the threshold for long-term potentiation (LTP) like plasticity [29, 30]. Thus, cathodal tDCS may lower the threshold for LTP-like plasticity during SLT which may then enhance language recovery [26]. On the other hand, online cathodal tDCS could improve behavioral performance by suppressing neuronal noise and enhancing the relevant neuronal signal [26]. Thus, if we want to maximize the impact of tDCS as an adjuvant to SLT, the role of timing and brain state needs to be considered.

It is presumed that the impact of tDCS is maximized when paired simultaneously with SLT (online tDCS). However, tDCS provided immediately before SLT (offline-before SLT) may also impact language recovery since it primes the language system at rest for subsequent language rehabilitation. It is also possible that tDCS after SLT (offline-after SLT) will aid in language recovery because it helps in memory consolidation and reconsolidation. The question of whether online tDCS and offline tDCS impact language recovery after post-stroke aphasia differentially has not been investigated to date.

## Aims

The main aim of the study is to investigate the differential effects of offline and online tDCS on language recovery in post-stroke aphasia. Specifically, we plan to conduct a randomized clinical trial (*N* = 48) in individuals with aphasia that compares the differential effects of tDCS delivered prior to, concurrent with, and following SLT.

## Method/design

### Study design

This is a randomized, parallel-assignment, double-blind exploratory treatment study. The exploratory randomized clinical trial will be conducted with 48 individuals with aphasia. Participants will be randomized to one of four treatment conditions (see below), with 12 participants per group. Participants will receive treatment 5 days a week for 3 weeks (i.e., 15 sessions). All participants receive 40 min of SLT. To equalize session length and maintain blinding, participants will also receive an additional 20 min of sham tDCS (see Fig. 1). The four treatment groups are as follows:Offline tDCS-before therapy (tDCS prior to SLT) — participants will receive 20 min of tDCS followed by 40 min of SLT. The session will end with 20 min of sham tDCS.Online tDCS (tDCS concurrent with SLT) — participants will receive sham tDCS for 20 min followed by concurrent SLT and tDCS. tDCS will be applied for the first 20 min of the 40-min SLT session. The session will end with 20 min of sham tDCS.Offline tDCS-after therapy (tDCS after SLT) — participants will receive sham tDCS for 20 min followed by 40 min of SLT. The session will end with 20 min of tDCS.Sham tDCS (only SLT) — participants will receive 20 min of sham tDCS followed by 40 min of SLT. The session will end with 20 min of sham tDCS. The sham tDCS group will serve as a control group and allow us to investigate the impact of SLT without tDCS.

**Fig. 1 Fig1:**
[figure not shown]
Treatment timeline by tDCS condition. **A** tDCS concurrent with the first 20 min of SLT, **B** tDCS prior to SLT, **C** tDCS post-SLT, and **D** sham tDCS (only SLT)

Subjects will be requested to come for a baseline session (3 to 4 h) before the treatment intervention begins. The baseline assessments may be done over two visits. In the baseline session, aphasia type and severity will be determined by the Western Aphasia Battery Revised (WAB-R) [31]. The WAB-R will be administered by a trained speech-language pathologist who is blind to the treatment group assignment. Participants will also perform baseline tasks of language and cognition in this session to further characterize their language and cognitive status.

Following the baseline assessment, all subjects who satisfy the inclusion criteria will participate in 3 weeks of the treatment intervention (i.e., 15 sessions). Subjects will be asked to return for an assessment immediately following the end of treatment and for follow-up testing 4 and 8 weeks after the end of treatment. The study schedule and assessments are shown in Table 1 and Fig. 2.

**Table 1 Tab1:** Trial schedule of enrollment, intervention, and assessments

	Study period					
	Enrollment	Allocation	Treatment intervention	Post-treatment assessment	Follow-up assessment	
Timepoint	***−t***_***1***_	0	***t***_***1***_	***t***_***2***_	***t***_***3***_	***t***_***4***_
**Enrollment**						
**Eligibility screen**	X					
**Informed consent**	X					
**Allocation**		X				
**Interventions**						
***Offline tDCS-before SLT***			X			
***Online tDCS-during SLT***			X			
***Offline tDCS-after SLT***			X			
***Sham tDCS-SLT only***			X			
**Assessments**						
***Western Aphasia Battery-Revised***	X			X	X	
***Wechsler Memory Scale-III***	X			X	X	
***Picture Description from Comprehensive Aphasia Test***	X			X	X	
***Apraxia of Speech Rating Scale***	X			X	X	
***Modified Rankin Scale***	X			X	X	
***Center for Epidemiologic Studies Depression Scale***	X			X	X	
***Communication Confidence Rating Scale For Aphasia (CCRSA)***	X			X	X	
***The Stroke and Aphasia Quality of Life Scale-39-Item Version (SAQOL-39)***	X			X	X	
***Philadelphia Naming Test***	X			X	X	
***Arizona Semantic Test***	X			X	X	
***Conners’ Continuous Performance Test II (CPT-II)***	X			X	X	
***Demographic data***	X					
***List of medications***	X

**Fig. 2 Fig2:**
[figure not shown]
Flowchart of the study timeline. Schematic diagram of the study protocol

### Setting

The study will be conducted at the Shirley Ryan AbilityLab, a rehabilitation hospital located in Chicago, IL.

### Ethical approval and trial registration

The study has been approved by Northwestern University IRB (STU00204900). The study is registered on the ClinicalTrials.gov website (ID: NCT03773406).

### Participants and recruitment

Flyers will be posted throughout the Shirley Ryan AbilityLab so that prospective subjects can contact the Center for Aphasia Research and Treatment if they are interested. Flyers will be sent to local speech-language pathologists and physicians so that potential participants can be informed. Participants from our previous studies who have given us permission to contact them regarding future studies will also be contacted. Interested participants can contact the Center for Aphasia Research and Treatment. Study personal will keep in regular contact with participants and their caregivers through phone/e-mail to ensure study retention. The study will be conducted in person at the research lab, thus ensuring adherence to intervention protocols. All protocol changes will be approved by the IRB. Participants cannot participate in other language treatment or brain stimulation intervention studies while participating in this study.

### Inclusion criteria

Participants will be included if they meet the following criteria: (a) diagnosis of fluent or non-fluent aphasia subsequent to a left-hemisphere infarct(s) confirmed by MRI or CT scan; (b) Aphasia Quotient on the WAB-R of 35–85; (c) at least 4 months post-onset of aphasia (this is beyond the stage of spontaneous recovery); (d) 18–80 years of age; (e) premorbidly fluent in English; (f) premorbidly right-hand dominant per the Edinburg Handedness Inventory; (g) visual acuity of 20/40 corrected; (h) auditory acuity no worse than 30 dB HL on pure tone testing, aided in the better ear; and (i) education greater than 12th grade.

### Exclusion criteria

Participants will be excluded if they have any other neurological condition (other than cerebral vascular disease) that could impact language and cognition such as Alzheimer’s disease, Parkinson’s disease, primary progressive aphasia, and traumatic brain injury. Participants will also be excluded if they have active substance use disorder or epilepsy.

### Sample size and power

The study will enroll a total of 48 subjects (12 in each group). Power calculations were based on our previous work with similar participants, and planned two-tailed analyses (*α* = .05) for the primary outcome measure, the simulated conversation on the trained script.

In preliminary work without tDCS, we observed improvement in trained script accuracy at the end of language treatment relative to baseline was 10.4% (SD = 8.2%). Assuming similar variability in the proposed study, *n* = 12 subjects per group will allow us to estimate changes in accuracy with precision (half-width of a 95% confidence interval) of ±5.2% in each group. In addition, a sample size of *n* = 12 subjects per group will provide 80% power with two-sided *α* = 0.5 for a two-sample *t*-test to detect a 9.9% difference in accuracy improvement between treatment arms and the sham treatment (e.g., improvement in accuracy of 10.4% and 20.3% in the two arms, respectively).

### Randomization

Participants will be randomized to each of the four treatment arms, i.e., four combination treatment sequences (tDCS prior to SLT, tDCS concurrent with SLT, tDCS following SLT, or sham tDCS (SLT only)). Randomization will be stratified by the baseline WAB-R AQ score (<60 vs. ≥60), and randomization will be conducted using the permuted block method. Randomization will be set by a statistician.

### Consent process

Informed consent will be obtained in a private office by a trained clinician/researcher who has experience with communicating with individuals with aphasia. They will ensure that subjects understand the purpose of the study, the procedures, and minimal risk and potential benefits associated with the study. The subjects will be made aware of their rights as research subjects (e.g., withdrawing at any point during the study without consequences). Subjects can take the consent forms home to review and consult with their family members prior to signing the consent forms.

## Intervention

### tDCS intervention

*tDCS parameters and intensity*: We will use 2mA of current intensity because it will yield higher current densities than 1mA or 1.5mA and may result in larger behavioral effects [6, 32]. *Duration*: Based on the duration of tDCS applied in previous studies [19, 24, 33], we will administer tDCS for 20 min. *Polarity*: There is no clear evidence that anodal tDCS improves behavioral performance while cathodal tDCS impairs behavioral performance [6, 14, 15]. However, a recent tDCS study [16] has shown that left-hemisphere cathodal tDCS elicits the most consistent language improvement in persons with aphasia. Thus, we will use left-hemisphere cathodal tDCS in our study. *Stimulation site*: There is no consensus on the optimal cortical site for tDCS in PWA [6, 24]. The choice for optimal site is complicated by lesion location and size and inter-individual differences in functional language reorganization post-stroke [6]. Recent advances have resulted in creating individualized montages based on factors such as current flow [34] and language outcomes prior to the treatment [16]. However, such methods are costly and time consuming and not viable if tDCS is seen as a low-cost adjuvant to language therapy. To circumvent this problem, we will target the left angular gyrus (AG) for stimulation. The AG has been implicated in multiple functions such as semantic processing, reading and comprehension, attention, and memory retrieval [35]. It is located at the junction of occipital, temporal, and parietal lobes [35]. Connectivity analyses have shown that AG is a hetero-modal hub linking language and episodic memory areas in the frontal, parietal, and temporal lobes as well as sensory and motor areas [36–38]. The rich functional and anatomical connectivity of AG with other brain regions and its role as a hetero-modal hub make it an ideal site for tDCS stimulation [39]. Stimulating a hub can increase functional connectivity with other brain regions and maximize the impact of tDCS [39]. It is possible that some persons with aphasia may have complete damage to the left AG and cannot be targeted by tDCS. To circumvent this problem, we will target the tissue area most proximal to the left AG. *tDCS implementation*: We will deliver 2mA of direct current for 20 min using a constant current stimulator (Soterix Medical., New York, USA) via a 15-cm^2^ saline-soaked sponge. To stimulate the left AG, a 15-cm^2^ cathodal electrode will be placed over CP5 according to the 10–20 international EEG system for electrodes. The electrode will be secured in position by a custom-built EEG cap http://www.easycap.de/ that will be marked with the location for AG. We will then confirm that the cathodal electrode is over left AG and not dead tissue through the use of a neuronavigation system (eXimia 3.1, Nexstim Ltd., Helsinki, Finland). The neuronavigation system allows us to co-register subjects’ heads in 3-D space with their T1-weighted MR images. The neuronavigation system identifies the scalp coordinates on the cortex and then maps the computerized picture of the scalp to the physical location on the person (see Fig. 3). Since tDCS requires two electrodes, the anodal “return” electrode of 25cm^2^ will be placed on the center of the supraorbital region. A larger return electrode was chosen to lessen its effect since recent studies have indicated that the return electrode may also provide some electrical stimulation to the cortex [35] .

**Fig. 3 Fig3:**
[figure not shown]
Example of target electrode location. Subjects’ heads are co-registered with MR images in a 3-D space to identify target location for the tDCS stimulation site. The red dot denotes the location of the target tDCS electrode

At the beginning of the tDCS, the current will be slowly increased (ramp-up) during the first 30 s until it reaches 2mA. The ramp-up process will allow the participants to acclimate to tDCS-induced sensations (e.g., itching). At the end of the tDCS session, the current will be slowly ramped-down in the last 30 s to 0mA. The total duration of the 2-mA direct current will be maintained for 20 min.

For the sham tDCS, the tDCS stimulation will be given for 30 s and then the tDCS device will be turned off. The 30-s stimulation will produce tDCS-induced sensations so that participants will not be aware when the tDCS is turned off.

### Language treatment

We will use *a standard-of-care treatment — script training —* to provide language therapy to the subjects [40–42]. The scripting treatment will be delivered by a computer program that provides script training in an interactive conversational context. Script training involves participants repeatedly practicing (e.g., pointing and choral reading) sentences within different contexts as either a dialogue or a monologue. The advantage of using *AphasiaScripts®*, a computer program with a virtual therapist instead of a human therapist, is that it removes extraneous variables associated with the human therapist. For example, it is possible that a human therapist might show differential levels of encouragement to different subjects and thus impact treatment fidelity. However, a virtual therapist will be consistent in providing the speech-language therapy across participants. Additionally, the program tracks every response and records choral and independent verbal productions that can be scored later by an unbiased clinician. Scripts will be ten sentences long and developed from common templates on the topics of buying a lottery ticket and watching a sporting event [40]. Examples of single sentence practice and conversational script practice from the AphasiaScripts® software are shown in Fig. 4.

**Fig. 4 Fig4:**
[figure not shown]
The AphasiaScripts software. **A** Example of a single conversational sentence. The highlighted word reflects the word that is being read aloud by the participant. **B** Example of a full conversation that participant practices with PAT (virtual therapist) and YOU (participant). Highlighted sentences reflect what the participant is practicing

### Blinding

In order to achieve blinding, a speech-language pathologist who is not directly associated with protocol administration and blind to the group assignment will administer and score all the assessments. Participants will also be blind to the timing of tDCS. In sham tDCS, the direct current is applied for 30 s and then the tDCS is switched off. The 30 s of stimulation does not induce any neural or behavioral changes, but participants feel the sensations associated with tDCS. In the online tDCS arm, sham tDCS will be applied at the beginning or end of the session. There is also a sham tDCS arm in which participants will not receive tDCS; they will receive only 40 min of SLT.

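### Only the online arm has felt stimulation during speech therapy, so participant blinding to timing is not assured for the online contrasts, which carry the main aim

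*Protocol article*

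**What the plan says.** The protocol article's Study design section labels the trial double-blind and gives sham stimulation two jobs: to make sessions equally long and to preserve blinding. It then sets out the four sessions.

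- Before arm: "participants will receive 20 min of tDCS followed by 40 min of SLT. The session will end with 20 min of sham tDCS".
- Online arm: "participants will receive sham tDCS for 20 min followed by concurrent SLT and tDCS". It adds that "tDCS will be applied for the first 20 min of the 40-min SLT session", and that a further 20 min of sham closes the session.
- After arm: "participants will receive sham tDCS for 20 min followed by 40 min of SLT. The session will end with 20 min of tDCS".
- Sham arm: "participants will receive 20 min of sham tDCS followed by 40 min of SLT. The session will end with 20 min of sham tDCS".

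The Blinding section says: "Participants will also be blind to the timing of tDCS". For the online arm it says: "In the online tDCS arm, sham tDCS will be applied at the beginning or end of the session".

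The tDCS intervention and Blinding sections explain the masking. Sham is 30 s of current, given so that participants feel what stimulation feels like. Active stimulation starts with a 30-s ramp-up that also produces sensations, such as itching.

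**The concern.** Masking by sham works when every arm feels the same thing at the same times. Here sham fills the slots before and after therapy but not the slot that defines online timing. The sensation that makes the before, after and sham arms alike is what sets the online arm apart.

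At stake is the comparison the trial exists to make. The Aims section puts online versus offline stimulation first, and the Background notes a common presumption that stimulation works best when given together with therapy. A participant who shared that view and noticed stimulation during practice might try harder or expect more. The primary outcome is live speech in a simulated conversation, so effort and expectation have a route to it. If the report calls the trial double-blind without qualification, readers will give the online contrasts a protection that the session layout does not provide.

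**Working it through.** No figure in the plan describes masking, so there is none to reproduce. The check lists stimulation onsets by arm from the Study design section and compares them with the Blinding section.

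**Inputs.** Slots of 20 min before SLT, 40 min of SLT and 20 min after SLT; 15 sessions; 12 participants in each of four arms (Study design). Active and sham onsets are both felt (tDCS intervention; Blinding).

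**Step 1: layout under Study design.** Session length is 20 + 40 + 20 = 80 min in every arm.

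| Arm | Minute 0 | Minute 20 (SLT starts) | Minute 60 (SLT ends) | Onsets during SLT |
|---|---|---|---|---|
| Before | active | none | sham | 0 |
| Online | sham | active | sham | 1 |
| After | sham | none | active | 0 |
| Sham | sham | none | sham | 0 |

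**Step 2: in-therapy onsets over the course.** Online: 1 × 15 = 15. Each other arm: 0 × 15 = 0.

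**Step 3: does the result depend on the sham wording?** Study design puts online sham at the start and at the end of the session. The Blinding section puts it at one or the other.

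- Start and end: total onsets are 3 × 15 = 45 online, against 2 × 15 = 30 in each other arm.
- One or the other, read literally: total onsets are 2 × 15 = 30 online, against 30 elsewhere, and the online session lasts 20 + 40 = 60 min.
- On both readings the in-therapy count is 15 against 0. The point rests on this count, not on the totals.

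**Step 4: which contrasts are affected?** Four arms give 4 × 3 / 2 = 6 pairwise contrasts. The online arm, 12 of 48 participants, enters three: online versus before, online versus after and online versus sham. In the other three, both arms have felt onsets at minutes 0 and 60 only, so the layout masks them from one another.

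**Step 5: compare with the claim.** The Blinding section asserts blindness to timing for all participants. The layout supports it among the before, after and sham arms and does not assure it for the online arm.

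**The case against.** The strongest reply is that this is a parallel-group trial. Each participant experiences one layout and never sees another. An online participant feels sham as well as active onsets, and feeling an onset does not show which one is active. To infer the arm, that participant would have to know that stimulation during therapy happens in one arm only. What participants are told is not shown. This objection stands: a reader might infer that online participants can identify their arm at every session, and the document does not support that. It shows that the felt pattern differs, not that anyone decodes it. But an unqualified blinding claim should not depend on participants not knowing the other layouts.

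The second reply is that other safeguards are strong. A speech-language pathologist blind to group administers and scores the assessments. Therapy comes from a virtual therapist, chosen so that encouragement does not vary between participants. The outcome is scored performance, not self-report. This also stands, and it narrows the remaining route to participant expectation or effort, which none of these safeguards closes.

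Third, a reader might take the looser wording in the Blinding section to mean that a 60-min online session gives the arm away. That is strained. Study design is explicit that the online session ends with sham and that session lengths are equalized, and a participant with one session type has no other length for comparison. The two sections still need to agree.

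Fourth, a reader might suppose that one arm practises under continuous itching. The protocol treats sensation mainly as an onset event to which participants acclimate, so the document supports a difference in onset pattern and no more.

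Finally, Fig. 1 is not shown. Its caption and the text mention no sham during SLT outside the online arm.

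**Conclusion.** The concern holds in limited form. By the protocol's own schedule, the online arm has 15 in-therapy stimulation onsets per participant and every other arm has none, on either reading of the online sham placement. Participant blinding to timing, and the double-blind label so far as it covers participants, are therefore not assured for the three online contrasts, including online versus offline.

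This rests on two things: the protocol's statement that active and sham onsets are both felt, and a schedule with no sham during SLT in the other arms.

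Two stronger conclusions are not supported. Blinding does not fail across the trial, because before, after and sham remain masked from one another and outcome assessment is blinded. Nor can a bias be put in accuracy points or as a share of the 9.9% detectable difference, because nothing in the document anchors its size. In an exploratory trial this is a matter of correct claims and reporting, and it does not invalidate the comparison.

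**What to change.** 1. Reconcile the Blinding section with the Study design section on where online sham is given.
2. Limit the participant-blinding statement to the before, after and sham arms. Qualify the double-blind label to match, and report the online contrasts as not assured to be participant-masked.
3. Add one allocation-guess item to the aphasia-friendly sensation questionnaire already planned in the Safety section, and report the answers by arm. With 12 per arm this is descriptive. It shows whether the different felt pattern led to different guesses.

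These need wording changes and one questionnaire item. The item can reach only participants who can still be asked.

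4. For participants not yet treated, the sponsor should reconcile the sham layout with the blinding claim, for example by considering whether the existing sham can also cover the SLT slot in the other arms. That is the sponsor's decision and the point does not depend on it. Recruitment began in 2018 and is expected to finish by 2023, so a change now would leave two sham layouts within groups of 12. Each participant's layout would have to be recorded and flagged in the analysis. If the layout stays as it is, items 1 to 3 are enough to make the claim match the design.
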